## Abstract

**Introduction:**

In resource-limited countries, people with disabilities seem to be particularly vulnerable to HIV infection due to barriers to accessing information and services, frequent exposure to sexual violence and social exclusion. However, they have often been left behind in the HIV response, probably because of the lack of reliable epidemiological data measuring this vulnerability. Multiple challenges in conducting good quality epidemiological surveys on people with disabilities require innovative methods to better understand the link between disability and HIV. This paper describes how the design and methods of the HandiVIH study were adapted to document the vulnerability of people with disabilities to HIV, and to compare their situation with that of people without disabilities.

**Methods and analysis:**

The HandiVIH project aims to combine quantitative and qualitative data. The quantitative component is a cross-sectional survey with a control group conducted in Yaoundé (Cameroon). A two-phase random sampling is used (1) to screen people with disabilities from the general population using the Washington Group questionnaire and, (2) to create a matched control group. An HIV test is proposed to each study participant. Additionally, a questionnaire including a life-event interview is used to collect data on respondents’ life-course history of social isolation, employment, sexual partnership, HIV risk factors and fertility. Before the cross-sectional survey, a qualitative exploratory study was implemented to identify challenges in conducting the survey and possible solutions. Information on people with disabilities begging in the streets and members of disabled people's organisations is collected separately.

**Ethics and dissemination:**

This study has been approved by the two ethical committees. Special attention has been paid on how to adapt the consenting process to persons with intellectual disabilities. The methodological considerations discussed in this paper may contribute to the development of good practices for conducting quantitative health surveys on people with disabilities.

**Trial registration number:**

NCT02192658.

Strengths and limitations of this studyLimitations include the difficulties to identify people with disabilities due to the limitation of the screening tool and the absence of a single and objective definition of disability.Strengths include the complex random sampling method to prevent selection bias;This study presents the use of a life-event history approach to understand the life trajectories of people with disabilities and how it relates to their vulnerability to HIV and the use of innovative communication methods to conduct the interviews that will improve the quality of data collected and decrease the risk of bias.

## Background

As highlighted during the 2014 International AIDS Conference held in Melbourne, there will be no ending of the HIV epidemic without closing the gap between people included in the global AIDS response and those left behind.^1^ In many resource-limited countries, people with disabilities are believed to be highly vulnerable to HIV infection;^2^
^3^ many face multiple barriers to access HIV and sexual and reproductive health (SRH) information.^4–9^ A growing body of evidence shows that people with disabilities are more likely to be victims of violence and abuse, which have been shown to be significantly associated with an increased risk of HIV infection.^2^
^10–13^ Disadvantages such as a lack of education and resources as well as social exclusion that are often experienced by people with disabilities in resource-limited countries have a negative impact on their ability to maintain good health. These factors and others contribute to creating a global risk environment.^14–16^ Although this vulnerability was first recognised 10 years ago and stressed in several international statements,^17–22^ people with disabilities have often been left behind with regard to the prevention and treatment of HIV/AIDS.^1^
^13^
^23^ A potential explanation for that is the lack of reliable epidemiological data measuring this vulnerability. Results from various reviews including a recent meta-analysis of studies conducted in Sub-Saharan Africa suggest that adults with disabilities have at least the same risk of HIV infection compared to the general population in this part of the world.^2^
^3^
^24^
^25^ However, given the limited quality of available studies and the variety of methodologies used,^24^ more epidemiological research is needed to establish firm evidence and to better understand the complex links between disability and HIV in order to help decision-makers prioritise their interventions. This paper presents the HandiVIH study design, as well as the methodological challenges of research aiming at providing such quantitative evidence.

### Multiple definitions of disability and implications for research

According to the World Report on Disability, people with disabilities represent around 15% of the world's population, with 80% living in resource-limited countries.^13^ However, large variations in disability prevalence are observed between studies, which could be explained by the different definitions of disability used.^26^ Disability is complex, dynamic and multidimensional.^13^
^27^
^28^ As a result, instead of a single, objective and easy-to-measure definition of disability, there are multiple approaches that only partially overlap.^29^
^30^ The medical approach that prevailed for decades focused only on impairments and their causes. This approach has been challenged by people with disabilities and several academic writers.^31^ A conceptual shift was operated through the social model in which people are viewed as being disabled mainly because of environmental barriers that prevent full participation in society.^32^ Integrating all these thoughts, the so-called ‘bio-psycho-social’ model promoted by the WHO proposes that disability is constructed of three connected components (impairments, activity limitations and social participation restrictions), and results from the interaction between individuals and environmental factors.^13^
^33^ This model requires different levels of information (individual, micro and macro environment) to capture the disability experience, and necessitates that researchers use and combine different methods and approaches.

### People with disabilities—a hard-to-survey population

People with disabilities living in resource-limited settings can be considered as a hard-to-survey population because of the technical challenges in identifying them,^34^ difficulty in establishing a sampling frame, and the existence of widespread exclusion mechanisms. Most studies available on HIV try to overcome such difficulties by using non-probabilistic sampling methods such as ‘snowball’ sampling.^35^ However, these methods do not allow for valid statistical inferences and lead to selection biases. One available alternative is a two-phase random sampling design with people with disabilities screened from the general population during the first phase and their eligibility confirmed during the second phase.^36^
^37^ However, particular attention needs to be paid to the screening questionnaire that should have acceptable sensitivity, specificity, validity and accuracy.^36^
^38^ This could be challenging in the context of disability. First, the wording of questions can create stigma and, as a result, people may be reluctant to identify themselves as disabled, or household members may experience shame at having a member with a disability and thus avoid identification.^39^ Second, the questions themselves may identify some disability types better than others. Third, the research communication process itself may be inaccessible for some groups of people with disabilities such as those with intellectual disabilities or the deaf-blind.

### Methods to investigate the vulnerability of people with disabilities

The vulnerability of people with disabilities to HIV and SRH adverse outcomes might be multifactorial, involving individuals as well as contextual factors that occur at different times during their life course. Therefore, to understand the link between disability and HIV infection, it is necessary to move beyond a static cross-sectional analysis and adopt a life-course approach. Such an approach aims to collect information on events and experiences over the lifetime, in order to identify sequences of risks and patterns of life-course trajectories, and to examine their association with health outcomes.^40^
^41^ Although longitudinal studies are the gold standard approach for life-course research, they are difficult to implement in low-income contexts, particularly because of high sample attrition and relatively high implementation costs. Alternatively, retrospective life-course studies have been shown to be useful and to provide data with adequate accuracy.^42–44^

### Objectives and assumption of the HandiVIH study

This study aims at improving our understanding of the situation of people with disabilities in Sub-Saharan Africa in relation to HIV and their SRH. The primary objectives of this study are to compare quantitatively the risk of HIV infection among people with disabilities to those without and to analyse the factors associated with their vulnerability to HIV. To do that, the study will (1) compare the HIV prevalence among people with disabilities and matched controls, (2) explore in detail their life-course events and knowledge, attitudes and practices, as well as (3) their access to information/services in relation to HIV and SRH, including their ability to negotiate safer sex and their exposure to violence. As the social environment is thought to be an important determinant of the vulnerability to HIV,^45^
^46^ the study will examine some aspects of people with disabilities' social environment, namely their social network and social participation.

Additional information on people with disabilities will be obtained through two substudies assessing people with disabilities begging in the streets and those who are members of disabled people's organizations (DPO). They aim to explore the boundary of the main study population and to assess the vulnerability to HIV of people with disabilities from these two groups.

## Methods and design

### Study strategy and design

This research project aims to combine qualitative and quantitative data on people with disabilities (figure 1). The quantitative component, a cross-sectional survey currently conducted in Yaoundé (Cameroon), constitutes the backbone of the research. Additional data—qualitative and quantitative—will complement the backbone component, providing complementary insight on the research question. An initial exploratory qualitative survey has been implemented to inform the subsequent quantitative work. Other qualitative research will be conducted after the quantitative survey to explore in more detail some of the quantitative findings. The two substudies on people with disabilities begging in the street and from disabled people's organisations use an exploratory quantitative design (see below).

**Figure 1 BMJOPEN2015008934F1:**
[figure not shown]
Study strategy.

Since the second qualitative research will be defined only after the analysis of the quantitative data, this article focuses on the cross-sectional component of the study, along with the exploratory work, and the two substudies.

Recruitment started in October 2014 and the estimated date of the last participants’ recruitment is November 2015.

### Backbone cross-sectional component

#### Washington group questionnaire (screening instrument)

To overcome the practical and conceptual difficulties in measuring disability, a group of experts set up by the UN Statistical Commission has proposed an operational tool for the identification of people with disabilities in surveys with good accuracy and reproducibility from one setting to another.^26^
^47^
^48^ This tool based on the International Classification of Functioning, Disability and Health (ICF) framework, includes a small number of questions covering six functional domains or basic actions: seeing, hearing, walking, cognition, self-care and communication. Each question asks the respondent to rate on a four-point scale how much difficulty he/she has experienced in the domain (see online supplementary appendix A). The Washington Group questionnaire is available in various forms; a short set questionnaire includes six questions and is recommended for use in national survey because of its simplicity. Additional questions are available from the extended set to supplement those from the short set and provide more detail on functional limitations.

##### Study population

All people aged 15–49 years with severe difficulties in at least one domain or some difficulties in at least two domains of the Washington Group questionnaire are considered as living with disabilities and therefore are eligible for the study.^47^
^48^ For each person with a disability included in the study, a control of similar age group (within a range of 5 years) and sex, living in the same enumeration areas and without functional limitation criteria is also recruited.

##### Sampling methods and disability screening

The sampling procedure consists of two phases. In the first phase, 177 enumeration areas in Yaoundé were drawn from the national sampling frame provided by the Central Bureau of the Census and Population Studies. Each drawn enumeration area is enumerated again in an exhaustive way to update the data. In the second phase, up to 200 households are randomly selected in each of the enumeration areas. All members of the selected households aged 15 years and above are then screened for disability using eight questions from the Washington Group disability questionnaire (six questions from the short set and two additional questions from the extended set, see online supplementary appendix A).^47^
^48^ The two additional questions from the extended set were included in the screening tool to better capture people with intellectual and/or mental disabilities.

##### Sample size

Sample size was computed to detect with a power of 80% and alpha risk at 5% a prevalence ratio >1.7 under the assumption that HIV prevalence in the controls is 6% in Yaoundé and that 10% of the participants may refuse the HIV test. A total of 850 persons with disabilities and 850 controls will be recruited. With this sample size, it is expected that each subgroup defined by impairments (hearing, visual, mobility, intellectual/mental) will include at least 100 participants. This is based on the assumption that the smallest subgroup will constitute at least 12% of the study population as it has been observed in other studies.^49^
^50^

##### Outcomes

*HIV prevalence*: The primary outcomes are the prevalence of HIV among people with disabilities and the prevalence ratio compared to the control group. Prevalence and prevalence ratio will also be computed for subgroups defined by the following impairments: (1) hearing (2) visual (3) mobility (4) intellectual/mental.

*Knowledge, attitude and practices (KAP):* Knowledge, attitudes and practices on HIV and AIDS, sexuality and reproductive health are assessed by questions derived from the ‘Illustrative questionnaire for interview-survey with young people’ designed by Cleland *et al*.^51^ In addition, main events of their sexual and reproductive life are recorded during the life-event interview.

*Disability*: Given its complexity, two dimensions of disability, activity limitation and social participation restriction, are examined. The extended set of the Washington Group disability questionnaire is used to assess activity limitation.^48^ Although social participation is central to the definition of disability, there are many challenges in measuring social participation as defined in the ICF framework.^52–55^ Much of the issues result from the lack of a consensual definition of the social participation construct.^55^ In this study, difficulties in participation in community/family events and in the decision-making process are rated on a four-point scale using questions based on the work by SINTEF^56^ and Handicap International.^57^

*Environmental factors*: Questions derived from SINTEF's work based on the validated Craig Hospital Inventory of Environmental Factors (CHIEF) Short-Form are used to assess the effect of environmental factors on functioning and social participation.^58^
^59^ Social support is assessed for all participants using questions adapted from the social network index.^60^

*Life-course trajectories:* Detailed information on the participants’ environment, history of employment, resources, relationships and reproductive health is collected during the life-event interview (see online supplementary annex B). It provides important information on the ‘life-situation’ aspects of social participation as mentioned in the ICF.^33^ It will be used to compare life-course trajectories between people with and without disabilities as well as people with disabilities across different types of impairments and their potential association with HIV status and adverse SRH outcomes.^61^

*Health services utilisation*: A short set of questions is used to determine the nature of SRH services used by the study respondents. Satisfaction with the last service used is also assessed. This topic will be investigated in more depth during the forthcoming qualitative component of the survey.

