##### Interviews and methods

Face-to-face interviews are organised with eligible participants identified from the screening stage after informed consent is granted. These interviews are conducted in a confidential environment in the participants’ homes or in a specific place set by study interviewers specifically trained for this purpose. Eligibility of the participant is first confirmed with the Washington Group questions: participants eligible as people with disability are asked additional questions from the extended Washington Group set (17 questions) to have more details on their functional limitation while controls are asked the same eight questions from the Washington Group questionnaire as part of the quality control.

After eligibility is confirmed, the full interview is proposed to the person. It includes a life-event interview on participants’ history of social participation, employment, resources, sexual partnership and fertility using the life-grid method.^43^
^62^ The life-grid is made of two A3 sheets divided into several columns (see online supplementary appendix B). The vertical axis represents the time; the first column gives time in years from birth to current year, the second column gives the age from 0 to current age and the third column gives the time elapsed. The other columns are used to report events according to their nature (people with whom the participant lived, main occupations/activities, resources, quality of life, sexual relationships, periods of transactional sex or sexual violence, pregnancies, children and disability onset). In addition, the occurrence of ‘important’ events is recorded as well as any information provided by the participants on the meaning of the events that occurred during his/her life. The life-grid helps to recall and structure the history of life events into chronological categories by cross-referencing the events. The grid is continually shown to the study participants as biographical information is recorded by the interviewer. The interview also includes closed questions on the participants’ characteristics, activity limitations, knowledge, attitudes and practices on HIV and SRH, environmental factors, social support and participation.

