Another major challenge of this study is to get a better understanding of the mechanisms explaining the vulnerability of people with disabilities to HIV. It should be emphasised that the cross-sectional design of the study precludes any firm causal conclusion as could be done in a prospective cohort. However, the life-course approach used in the study may provide us with important information. The strength of the life-course approach lies in its ability to provide a comprehensive insight into the context, connecting sexual risk behaviour to other social factors and looking at events with an adequate time perspective.^76^ The life course perspective is particularly important in the context of people with disabilities who experience disadvantages that accumulate throughout the life.^77^ Besides, the life-grid method for collecting biographical information has been shown to improve the recall and thereby the accuracy of collected data.^44^ Retrospective data collection might not be as accurate as in prospective studies, although it was shown to provide information with good validity and reliability for some types of events.^78–80^ Moreover, the subjective assessment of events and life circumstances during the life-event interview is important information that may contribute to a better understanding of the life situation of people with disabilities and its relation to HIV risk. Interestingly, the life-event method gives more attention to the respondents’ perspective. Owing to this opportunity offered to respondents to account for their lives, the life-event method creates an environment conducive for sharing intimacy, which contributes to improving the quality and wealth of the data. It also gives the possibility to combine individual and social data. Although possible, the use of the life-grid method with people with intellectual disabilities is challenging. In our experience, a third person close to the respondent has to help in answering to the environmental activities and resource modules. Nevertheless, for most of this specific disabled population, the training of the interviewers as well as the use of the communication tools (pictograms, dolls) has allowed the collection of intimate data without the help of a third person, preventing the proxy bias in important topics such as sexuality and intimate relationships.

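### The primary HIV prevalence ratio can exceed 1 through limitations caused by HIV itself, and no planned analysis of the ratio uses the recorded date of disability onset

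*Protocol article*

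**What the plan says.** All references are to the protocol article.

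- **Objective.** The Objectives section sets out to "compare quantitatively the risk of HIV infection among people with disabilities to those without", and lists the comparison of HIV prevalence with matched controls as the first step.
- **Outcome.** Under Outcomes: "The primary outcomes are the prevalence of HIV among people with disabilities and the prevalence ratio compared to the control group". The only subgroups named for this ratio are impairment types.
- **Who counts as disabled.** Under Study population, on the Washington Group questions: "All people aged 15–49 years with severe difficulties in at least one domain or some difficulties in at least two domains". There is no criterion on cause or date of onset.
- **Who can be a control.** A person of the same sex and similar age, "living in the same enumeration areas and without functional limitation criteria is also recruited".
- **What is recorded.** Under Interviews and methods, the life grid has a time axis in years and in age, and its columns include "sexual relationships, periods of transactional sex or sexual violence, pregnancies, children and disability onset".
- **What is analysed.** Statistical analysis plans weighted prevalence estimates with design-adjusted intervals, multilevel regression for HIV risk factors (including life-course characteristics), multistate models and sequence analysis. None of these is tied to disability onset in the prevalence ratio.
- **What is conceded.** The Discussion says that "the cross-sectional design of the study precludes any firm causal conclusion as could be done in a prospective cohort".

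**The concern.** The ratio compares current HIV status between groups formed by current functional status. If HIV disease leaves some people with difficulty seeing, walking, remembering or caring for themselves, they meet the disability cut-off because they are infected. The same cut-off excludes them from the controls. Both effects raise the ratio without any difference in the risk of acquiring HIV.

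This matters because the objective speaks of risk of infection and the Discussion expects the findings to inform decision-makers. An excess due to greater exposure and an excess due to disability following HIV call for different readings, and the overall ratio cannot tell them apart. The material for a partial separation is already collected, since onset is dated on the grid, but the stated analysis of the ratio does not use it.

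**Working it through.** **Inputs from the Sample size section:** control prevalence 6%, target ratio 1.7 (so 10.2% in the disabled group), 80% power, 5% alpha (taken as two-sided), 10% test refusal, 850 per group. Tested per group: 850 × 0.9 = 765.

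**The plan's own figure.** The pooled two-proportion formula is n = [1.96·√(2·p̄·(1−p̄)) + 0.842·√(p₁(1−p₁) + p₂(1−p₂))]² / (p₂−p₁)², with p₁ = 0.06, p₂ = 0.102 and p̄ = 0.081. It gives 662 tested, and 662/0.9 = 736 recruited per group. Other two-sided variants give 724 to 788. The stated 850 is not reproduced but is larger than needed: 765 tested gives 85.4% power for 1.7. This is conservative and does not bear on the point.

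**Ratio with no excess acquisition risk.** Let s be the share of the disabled group whose limitation is due to HIV, and give the rest the control prevalence. Then p = s + (1−s)·0.06, the ratio is p/0.06, and the share of that group's infections that caused the disability is s/p. The values of s are assumptions; the documents give none.

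| s | p | Ratio | Share of the group's infections | Chance of a significant result, 765 per group |
|---|---|---|---|---|
| 1% | 0.0694 | 1.16 | 14% | 11% |
| 2% | 0.0788 | 1.31 | 25% | 30% |
| 3% | 0.0882 | 1.47 | 34% | 56% |
| 4.5% | 0.102 | 1.70 | 44% | 85% |

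The last row solves s = (0.102 − 0.06)/0.94 = 4.47%, about 34 of 765 tested, against 0.102 × 765 = 78 infections in all. The last column uses a simple two-sample approximation that ignores clustering and matching.

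**The same mechanism from the population side.** Let d be the prevalence of disability unrelated to HIV and q the chance that an infected person without prior disability develops a limitation from HIV. Overall prevalence h is set so that controls are at 6%: h = 0.06/[0.94(1−q) + 0.06]. Disabled-group prevalence is [d·h + (1−d)·h·q]/[d + (1−d)·h·q]. With d = 15% (the Background gives this as a world figure for all disability; none is given for Yaoundé) and q = 5%, h = 0.0630. Disabled-group prevalence is then 0.0794 and the ratio 1.32. For q = 2%, 5% and 10%, the ratio is 1.13, 1.32 and 1.67 at d = 15%, and 1.38, 1.93 and 2.84 at d = 5%. The values of q are also assumptions.

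**The opposite pull.** People disabled late may have had most of their exposure before disability. If a true ratio of 1.7 applies only to a fraction f with early onset, the overall ratio is 1 + 0.7f: 1.21 at f = 30% and 1.49 at f = 70%, with power 17% and 59%.

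**Both together.** With f = 50%, prevalence is 0.5 × 0.102 + 0.5 × 0.06 = 0.081. Adding s = 2% gives 0.02 + 0.98 × 0.081 = 0.0994, a ratio of 1.66. Against a true 1.7 in the early-onset half, the two nearly cancel.

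**Precision of an early-onset ratio.** If 40%, 50%, 60% or 70% of pairs qualify (an assumption), 306, 382, 459 or 536 are tested per group. Power for 1.7 is 48%, 57%, 65% or 71%. At 40% and 70%, the ratio detectable with 80% power is about 2.1 and 1.8.

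**The case against.** The strongest reply is that nothing is mis-stated. The outcome is a prevalence ratio and is a valid measure of burden among people now living with disability, whatever the cause. The Discussion concedes that causal conclusions are limited and offers the life-course approach in response. The planned regression and multistate models could take onset as an input, and a supplementary ratio might appear in an analysis plan that is not shown.

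Much of this stands. The ratio should be kept, and the general limit is acknowledged. What the reply does not meet is that the article fixes the objective as infection risk and the exposure as current difficulty, then attaches no analysis of the ratio to the gap between them. The caveat does not name disability caused by HIV.

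Second, the sizes are assumed. That also stands. A share of 4.5% sounds small, but it requires about 44% of the group's infections to have caused the disability.

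Third, a reader might infer that the ratio is biased upwards overall. The documents do not support this: late-onset dilution pulls the other way, and neither effect can be sized from the text. A reader might also suppose that distress after diagnosis triggers the two questions added for intellectual and mental disability. Their wording is in an appendix that is not shown, so the point does not rely on it.

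**Conclusion.** The point holds as a question of interpretation and of an unused variable. As defined, the primary ratio can exceed 1 with no excess risk of acquiring HIV, and it cannot by itself answer an objective about infection risk. With no true effect it would be 1.16, 1.31, 1.47 or 1.70 if 1%, 2%, 3% or 4.5% of the disabled group owed their limitation to HIV. Those shares are assumptions without a source in the documents. The mechanism and its upward direction are established; its frequency and the net direction of error in the overall ratio are not. It would go too far to call the primary outcome invalid or to replace it. This is a cheap improvement.

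**What to change.** Keep the overall ratio as the primary estimate of burden. Pre-specify a supplementary HIV prevalence ratio restricted to matched pairs whose disabled member's onset on the life grid was at birth or before one fixed age in childhood. Set that age before HIV results are analysed, and apply it without regard to the person's own sexual history. Restricting by pair keeps the age, sex and area matching.

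Do not split at the disabled member's own first sexual relationship. That would select late-debut or never-active people on one side of each pair only. It would also overlook sexual violence and transactional sex, which the grid records separately.

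Report the early-onset ratio beside the ratio for later-onset pairs, and interpret statements about vulnerability to infection in light of both. Say that an excess confined to later-onset pairs may reflect either direction; it should not be dismissed as non-vulnerability.

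State the limits: HIV infection is not dated, infection acquired in infancy is not separated, and recalled onset may be inexact.

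The cost is analysis-plan wording and one analysis on data already collected, with no new recruitment or questions. The supplementary ratio is less precise, as shown above; the overall ratio keeps its power.
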